## Trial design

This clinical trial was designed as a prospective, randomized investigator-initiated pilot trial to be conducted in one center. In all, 24 patients are intended to participate in the study after giving informed consent. The study design was reevaluated after the first three patients had passed the endpoint of the biomolecular and histological sampling. Since the first three patients required no adjustments post-treatment, it is feasible that for the treatment of the remaining 21 patients no further adjustments will be required.

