### Interventions

All 24 patients will have received the three abutments consecutively, each for a 1-month wearing period. The abutments are as follows: zirconia ceramic (Z) (Zenostar MO; Wieland Dental GmbH, Pforzheim, Germany; lot S13270); lithium disilicate ceramic (L) (IPS e.max Press; Ivoclar Vivadent, Schaan, Liechtenstein; lot S44695); titanium (T) (Zenotec Ti; Wieland Dental GmbH, Pforzheim, Germany; lot 20130305 4012). The sequence of the three materials is randomly assigned. The abutments are manufactured by luting hollow Z-, L-, or T-cylinders on Variobases™ (Straumann, Basel, Switzerland; lot: HE661/HK699) by means of Multilink® Hybrid Abutment cement (Ivoclar Vivadent, Schaan, Liechtenstein; lot: T10017). The abutments’ surface roughness is adjusted by polishing them to ensure conformity. The results are checked by Ra measurements of each abutment (Ra < 0.1 μm).

The examinations and specific data collection are shown in Table 1. Screening is performed before implantation to check the inclusion/exclusion criteria. Implantation is performed according to the standardized implantation procedure in the Department of Prosthetic Dentistry making use of the Straumann®-guided surgery implantation system (Straumann, Basel, Switzerland) in combination with an implantation template after three-dimensional implant planning (CoDiagnostix; Dental Wings GmbH, Chemnitz, Germany). Bone-level Straumann implants (SLActive, RC) are submerged.

**Table 1 Tab1:** Examinations and collected data

Examination type	Examination time	Collected data
Screening	Before implantation; every patient eligible for the study regardless of his/her participation in the trial	Checking of the inclusion/exclusion criteria
Implantation	Before inclusion in clinical trial	
Pretreatment examination	Before randomization	Clinical control of implant site; informed consent
Baseline: second-stage surgery and insertion of first abutment	90 ± 14 days after implantation	Tissue sampling (control punch biopsy)
		Photo documentation
		X-ray control
PICF sampling	7, 14, 21, and 28 (±1) days after insertion of the first, second, and third abutment	PICF sampling
		Plaque Index (PI)
		Gingival Index (GI)
		Probing depth (PD)
		Bleeding on probing (BOP)
Tissue sampling and insertion of second and third abutments	2–5 days after the last PICF sampling around the first, second, and third abutment	Tissue sampling (ring biopsy)

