### Sample size

The study is biometrically categorized as a pilot study because of the sample size of 24 patients. During establishment of the study design, there were no clinical results on which a biometrical sample size estimation could be based. The sample size has, therefore, been set at 24 patients. The weekly PICF sampling both buccally and lingually results in 24 PICF samples from each patient. Four histological specimens (one control punch biopsy and three ring biopsies) are to be collected from each patient.

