### Randomization

Randomization is performed with a threefold crossover design. The sequence of the three abutment materials is randomly assigned, resulting in six groups (ZLT, ZTL, LZT, LTZ, TZL, TLZ) with four samples for each. The study is stratified into the two gender groups.

Randomization concealment is ensured because a clinic staff member not involved in the clinical trial performs the allocation according to a randomization list.

Any eligible patient is recorded in a screening list maintained by the clinical investigators. Once a patient has given informed consent, a patient number and randomization are requested from the staff member performing the allocation according to the randomization list. The clinical investigator enters the patient number into the patient list, which also includes the appointments of each patient. The patient number and sequence of the abutment materials are transferred into the Case Report File of the baseline visit (second-stage surgery).

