Washout periods between the different abutment materials may help to exclude an influence of the preceding abutment material on the tissues. Washout periods may be performed either by wearing a “neutral” abutment for a specific time between the tested abutments or by permitting tissues to heal without an abutment and punch biopsy again before inserting the next abutment. Following discussion with biometricians, the additional punch biopsies and time on top of an already prolonged procedure were deemed ethically unjustifiable. In addition, the newly formed cells and tissue in direct contact with each abutment are most likely to be affected and are circularly removed by the stamping press. Thus, we renounced washout periods in the trial. However, an influence of the preceding abutment material on the biomolecular and immunohistochemical findings of the next abutment material cannot be fully excluded. To the author’s knowledge, there is no study which has tested this aspect yet. If our biometricians detect clear evidence of previous abutment influence (worst-case scenario) only the first abutment material (*n* = 8 for each abutment material) shall be used for analysis.

The study combines biomolecular and immunohistochemical analyses – both aiming to detect the same biomarkers – and clinical analyses. This design allows a site-specific correlation analysis between those two techniques for biomarker detection as well as clinical indices to monitor gingival health.

This study is the first randomized clinical trial to combine biomolecular, immunohistochemical, and clinical analyses to determine the environment around transmucosal abutments during wound healing in humans. Two well-established abutment materials (titanium and zirconia) are compared with a more recently introduced abutment material (lithium disilicate). A deeper understanding of abutment materials’ interactions with peri-implant soft tissue will help us comprehend the formation mechanisms of implant-associated complications and to develop prevention strategies.

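### The carryover rule switches to first-abutment data only (8 patients per material), although the balanced six-sequence design supports a carryover-adjusted analysis of all three periods at far smaller variance

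*Protocol article*

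**What the plan says.** - **Design.** The Randomization section says: "Randomization is performed with a threefold crossover design". The order of zirconia, lithium disilicate and titanium is random, "resulting in six groups (ZLT, ZTL, LZT, LTZ, TZL, TLZ) with four samples for each". The Interventions section adds: "All 24 patients will have received the three abutments consecutively, each for a 1-month wearing period".
- **Washout.** The Discussion explains that further punch biopsies and a longer procedure were judged ethically unjustifiable, and that the tissue most likely to be affected is cut away with the stamping press before the next abutment goes in. It concludes: "Thus, we renounced washout periods in the trial".
- **Carryover.** The same paragraph concedes that "an influence of the preceding abutment material on the biomolecular and immunohistochemical findings of the next abutment material cannot be fully excluded" and that no known study has tested this.
- **Rule.** "If our biometricians detect clear evidence of previous abutment influence (worst-case scenario) only the first abutment material", given as n = 8 per material, is then to be used for analysis.
- **Analysis.** The Statistical methods section describes an exploratory analysis with tests chosen by distribution. It also says that power and sample size for similar future studies will be worked out. It names no model terms.

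**The concern.** The set of data behind the primary comparison depends on what those same data show about carryover. The two branches differ greatly in what they can deliver. One compares materials within 24 patients; the other compares three groups of 8 different patients.

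The rule can therefore cost in two ways. If it triggers, rightly or by chance, most of the information is set aside. If carryover exists but the check does not find it, a default analysis without a carryover term gives biased material differences. Both matter for a pilot whose results are meant to inform later sample sizes: first-period data alone cannot supply the within-patient variance between periods that a later crossover would need.

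**Working it through.** **Inputs.** From the protocol: 24 patients (Trial design), three periods each (Interventions), six orders with 4 patients each (Randomization), 24 crevicular fluid samples per patient (Sample size), no washout and a fallback of n = 8 (Discussion). The protocol gives no SD, effect size, correlation or test level. The calculations therefore use SD units, a two-sided 5% level, one summary value per patient and abutment, and an assumed intraclass correlation (ICC) from 0 to 0.7.

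**1. The protocol's own figure.** Each material comes first in 2 of the 6 orders, so 2 × 4 = 8 patients per material. The stated n = 8 is reproduced.

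**2. What the fallback drops.** Abutment-periods: 24 × 3 = 72 planned, 24 kept, 48 dropped (two thirds). Fluid samples: 24 × 24 = 576 planned, 24 × 8 = 192 kept, 384 dropped.

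**3. Is carryover adjustment possible?** A least-squares model with patient (24 parameters), period (2), material (2) and first-order carryover (2) has 30 parameters. The design matrix has rank 30, leaving 72 − 30 = 42 residual degrees of freedom. Each ordered pair of successive materials occurs 8 times. The model is estimable.

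**4. Variance of a pairwise material difference** (σw² = within-patient variance):
- all periods, unadjusted: 2/24 = 0.0833 σw²
- all periods, carryover-adjusted: 0.1042 σw², that is 0.1042/0.0833 = 1.25 times; √1.25 = 1.118, so intervals are about 12% wider
- first abutment only: 2/8 = 0.25 times the total variance, that is 0.25/(1 − ICC) σw²

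Fallback relative to adjusted = 0.25/[0.1042 × (1 − ICC)] = 2.4/(1 − ICC):

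| Assumed ICC | Fallback variance ÷ adjusted variance |
|---|---|
| 0 | 2.4 |
| 0.5 | 4.8 |
| 0.7 | 8.0 |

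**5. Detectable difference at 80% power, all in total SD.** Fallback (standard error 0.5, 21 df): 1.47. Adjusted analysis: 0.93 at ICC 0, 0.65 at ICC 0.5, 0.51 at ICC 0.7. For a true difference of 1 total SD, the fallback has 48% power; the adjusted analysis has 86% at ICC 0 and 99% at ICC 0.5.

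**6. Missed carryover, if the default model has no carryover term.** Let one material have an effect of 0.75 within-patient SD and carry over half of it, 0.375. Each other material follows it in 8 of its 24 periods, so its mean rises by 0.375 × 8/24 = 0.125. The unadjusted difference becomes 0.75 − 0.125 = 0.625, about 17% too small; in simulated trials where an assumed check did not trigger, it averaged 0.62. With an assumed 10%-level check and ICC 0.5, the check triggered in 21% of such trials.

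**7. The rule as a whole, simulated with an assumed 5% or 10% check and an unadjusted default.** With no material effect and carryover of 0.5 to 0.8 total SD from one material, false positives were 5.9% to 9.2%, against about 5% for the always-adjusted model. With a 1 SD effect and 0.5 SD carryover, power was 66% to 83%, against 88% to 100%. With neither effect nor carryover, the overall error stayed at about 5%.

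**The case against.** **The rule is a backstop.** The protocol labels it a worst case, writes it down in advance and gives an ethical reason for omitting washout. The ring biopsy removes contact tissue before each change, all orders are balanced, and the Blinding section says analyses are masked. This stands. A reader might infer that the rule is the only protection against carryover; the documents do not support that. Masking does not, however, stop the data from deciding which periods are analysed.

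**Missing details may sit elsewhere.** A condensed article can leave the definition of convincing evidence, and the model terms, to an analysis plan that is not shown. This also stands. The lack of a threshold is not a fault in itself, and steps 6 and 7 are illustrations. What the article does fix is the consequence: a switch to the first abutment only. Steps 2 to 5 need no assumption about the check.

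**The fallback is not powerless.** A reader might conclude that it could detect no plausible difference. The protocol gives no effect size to support that, and power with 8 per group is about 82% at 1.5 total SD and 97% at 2.

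**The adjusted model is not a complete cure.** It assumes additive first-order carryover. If the 0.375 of step 6 persists at full strength into the period after next, the adjusted estimate is 0.61 instead of 0.75 (at half strength, 0.68). The unadjusted estimate does worse under the same pattern: 0.625 − 0.375 × 4/24 = 0.5625. First-abutment data are free of any carryover pattern, so that comparison is not superfluous. The objection supports keeping it as a fixed companion analysis; it does not support switching to it.

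**Conclusion.** The point holds as a weakness in a stated analysis rule. A data-triggered switch drops 48 of 72 abutment-periods and gives up the within-patient comparison, while the chosen design already supports a carryover-adjusted analysis of all periods for 1.25 times the unadjusted variance. The fallback has 2.4 to 8.0 times the variance of that analysis for ICC 0 to 0.7. The ICC range is assumed, and the adjusted analysis relies on additive first-order carryover. The bias figure (0.62 for a true 0.75) applies only if the default model omits carryover, which the protocol does not say.

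The main harm is lost precision, with bias where carryover goes unseen; the inflation of false positives is modest. The trial is an exploratory pilot with no confirmatory test, and the rule may never trigger, so this is something that should be fixed, not a defect that invalidates the trial.

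**What to change.** Replace the switching rule. State, before assay results are unmasked, that:

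1. all three periods are always analysed, with patient, period, material and a first-order carryover term in the model, and that term is fixed in advance and not turned on or off by a test;
2. the first-abutment-only comparison (n = 8 per material) is always reported beside it as a sensitivity analysis, whatever it shows, because it does not depend on the form of the carryover.

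The change is to wording only and needs no further patients, visits, biopsies or assays. Its price is intervals about 12% wider than in the unadjusted crossover analysis, paid even if there is no carryover, and reliance on the additive first-order form, which the second analysis helps to check.

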## Trial status

The screening and recruiting for the study began in August 2013 and is still ongoing. To date, the first eight patients have received a single-tooth implant. Five of the eight have finished the study.

## Abbreviations

BOP: bleeding on probing
CONSORT: Consolidated Standards of Reporting Trials
ELISA: enzyme-linked immunosorbent assay
GI: Gingival Index
IL-1β: interleukin-1β
L: lithium disilicate
MMP-8: matrix metalloproteinase 8
MRP: myeloid-related protein
PD: probing depth
PI: Plaque Index
PICF: peri-implant crevicular fluid
PMN-elastase: polymorphonuclear elastase
T: titanium
TBS: Tris-buffered saline
Z: zirconia
